# The effect of smartphone-based monitoring and treatment including clinical feedback versus smartphone-based monitoring without clinical feedback in bipolar disorder: the SmartBipolar trial—a study protocol for a randomized controlled parallel-group trial

**DOI:** 10.1186/s13063-023-07625-1

**Published:** 2023-09-12

**Keywords:** Bipolar disorder, Smartphone-based monitoring, Randomized controlled trial

## Abstract

**Introduction:**

A substantial proportion of patients with bipolar disorder experience daily subsyndromal mood swings, and the term “mood instability” reflecting the variability in mood seems associated with poor prognostic factors, including impaired functioning, and increased risk of hospitalization and relapse.

During the last decade, we have developed and tested a smartphone-based system for monitoring bipolar disorder. The present SmartBipolar randomized controlled trial (RCT) aims to investigate whether (1) daily smartphone-based outpatient monitoring and treatment *including* clinical feedback versus (2) daily smartphone-based monitoring *without* clinical feedback or (3) daily smartphone-based mood monitoring *only* improves mood instability and other clinically relevant patient-related outcomes in patients with bipolar disorder.

**Methods and analysis:**

The SmartBipolar trial is a pragmatic randomized controlled parallel-group trial. Patients with bipolar disorder are invited to participate as part of their specialized outpatient treatment for patients with bipolar disorder in Mental Health Services in the Capital Region of Denmark. The included patients will be randomized to (1) daily smartphone-based monitoring and treatment *including* a clinical feedback loop (intervention group) or (2) daily smartphone-based monitoring *without* a clinical feedback loop (control group) or (3) daily smartphone-based mood monitoring only (control group). All patients receive specialized outpatient treatment for bipolar disorder in the Mental Health Services in the Capital Region of Denmark. The trial started in March 2021 and has currently included 150 patients. The outcomes are (1) mood instability (primary), (2) quality of life, self-rated depressive symptoms, self-rated manic symptoms, perceived stress, satisfaction with care, cumulated number and duration of psychiatric hospitalizations, and medication (secondary), and (3) smartphone-based measures per month of stress, anxiety, irritability, activity, and sleep as well as the percentage of days with presence of mixed mood, days with adherence to medication and adherence to smartphone-based self-monitoring. A total of 201 patients with bipolar disorder will be included in the SmartBipolar trial.

**Ethics and dissemination:**

The SmartBipolar trial is funded by the Capital Region of Denmark and the Independent Research Fund Denmark. Ethical approval has been obtained from the Regional Ethical Committee in The Capital Region of Denmark (H-19067248) as well as data permission (journal number: P-2019–809). The results will be published in peer-reviewed academic journals, presented at scientific meetings, and disseminated to patients’ organizations and media outlets.

**Trial registration:**

Trial registration number: NCT04230421. Date March 1, 2021. Version 1.

**Supplementary Information:**

The online version contains supplementary material available at 10.1186/s13063-023-07625-1.

## Introduction

Bipolar disorder is characterized by recurrent alterations in mood, encompassing affective episodes of depression, (hypo)mania, and mixed episodes with intervening periods of euthymia [1]. Bipolar disorder is a disabling psychiatric disorder with a prevalence of 1–2%, a high risk of recurrence of affective episodes [2], a lifelong elevated risk of suicide, and a decreased life expectance of 8–12 years compared to the general population [3]. Bipolar disorder is a complex illness as patients present differently during manic, depressed, mixed, and remitted states, and also the treatment differs during these states. Despite current standard treatment, patients with bipolar disorder experience affective symptoms approximately half of the time, alternating between depressive episodes and manic episodes three times per year on average, while 10% suffer from permanent symptoms [4]. During the last decade, there has been a gradual shift from focusing on affective episodes to inter-episodic mood instability [5–8]. A substantial proportion of patients with bipolar disorder experience subsyndromal mood swings on a daily basis more than 50% of the time between episodes [8–10]. This mood variation (variability in mood registrations) is reflected as mood instability reflecting core psychopathology in bipolar disorder [9–12]. Furthermore, mood instability has been associated with increased perceived stress, decreased quality of life and functioning, and increased risk of relapse and hospitalization [9, 12–15]. In addition, mood instability has been suggested to be associated with biological measures of stress-hormone dynamics [16]. Due to the increased focus on the impact of mood instability, mood instability has been suggested as an independent treatment target and as a more sensitive outcome measure in randomized controlled trials (RCTs) than for example relapse or recurrence of affective episodes [7, 8, 11, 17, 18].

### A new organization for all patients with bipolar disorder: the Clinical Academic Group for bipolar disorder (the CAG Bipolar) in the Mental Health Services, Capital Region of Denmark

The present research group has initiated and conducted the first large pragmatic randomized controlled trial (RCT) covering the entire Mental Health Services, Capital Region of Denmark, in patients with newly diagnosed bipolar disorder investigating differences in effectiveness between specialized outpatient treatment and generalist treatment. The trial showed that *specialized* combined optimized pharmacological treatment, and group-based psychoeducation improved patient outcomes substantially in the early stages of bipolar disorder [19].

Inspired by experiences from the specialized Copenhagen Affective Disorder Clinic, and the King’s College/Institute of Psychiatry, London, the Mental Health Services, Capital Region of Denmark, decided to implement and test a new organization of outpatient treatment services for all patients with bipolar disorder who are not newly diagnosed, but in a more progressed state (secondary care facilities), in the Capital Region, a so-called Clinical Academic Group for bipolar disorder (the CAG Bipolar) starting from December 2019 [20]. Clinical Academic Groups (CAGs) bring together clinical services, research, education, and training to offer care and treatment that is based upon reliable evidence backed up by research (https://www.kcl.ac.uk/ioppn/depts/ps/about/cags/index.aspx). A major aim of the CAGs is to aid effective and rapid use of the latest research to improve the care and treatment provided.

### Smartphones as a new way to empower patients, treatment, and research

The rapid growth in access to and capabilities of digital health technologies presents a feasible route toward augmenting traditional mental healthcare and bridging the gap between the need for treatment and the capacity to deliver it. In addition, the rapid evolution and ubiquity of mobile networks have resulted in the increasing development of smartphone-based tools for remote and real-time self-monitoring [21, 22]. Smartphones provide a unique platform for fine-grained symptom monitoring and treatment. They are a convenient means of electronic self-assessment, allowing patients to record and review their data ubiquitously on-demand daily. The term “digital phenotyping” was introduced to mental health in 2015 [23] and has been defined as the “*moment-by-moment quantification of the individual-level human phenotype *in situ* using data from personal digital devices*” [24]. Digital phenotyping (both active (self-monitoring) and passive (sensor-based data)) refers to approaches in which personal data gathered from mobile devices and sensors is analyzed to provide health information on physiological functions or behavioral indicators [25, 26]. Digital phenotyping potentially uses smartphones to measure symptoms and behavior. These data can be seen as digital footprints or data traces arising as a by-product of interactions with technology. The rapid evolution and ubiquity of mobile technology have increased the development of tools for remote and real-time self-monitoring and treatment [27].

During the last decade, we have developed and tested a unique smartphone-based monitoring and treatment system, the Monsenso system for patients with bipolar disorder. The Monsenso system was initially developed by the IT University in Copenhagen in close collaboration with Copenhagen Affective Disorder Research Center (CADIC), Psychiatric Center Copenhagen, Mental Health Services, Capital Region of Denmark, involving a wide range of patients, clinicians, and researchers (in the EU funded MONARCA project [28, 29], the MONARCA II trial [30], and the RADMIS trial [31]). Using the Monsenso system for smartphone-based treatment of bipolar disorder has been shown to have a very high compliance rate (87–95%) and is considered useful by patients and clinicians helping patients to manage their course of illness [28–30]. Besides subjective monitoring, we have additionally shown that sensor-based data such as physical [32], social activity [33], and voice features [34, 35] reflect illness activity. The effects of the Monsenso smartphone system in patients with bipolar disorder have so far been investigated in three RCTs by the authors [29–31]. Overall, using the smartphone-based monitoring system resulted in increased quality of life, decreased perceived stress, and increased use of lithium without influencing the degree of depressive or manic symptoms. A recent systematic review and meta-analysis conducted by the International Society for Bipolar Disorders (ISBD) Big Data Task Force found no support that smartphone interventions may reduce the severity of depressive or manic symptoms in patients with bipolar disorder. However, the low number and high heterogeneity of studies supports the need for the use of more sensitive outcomes, such as psychiatric hospitalizations and mood instability [18].

### A window of opportunity

This is the first time that large-scale treatment with smartphones in clinical practice will be introduced and investigated as part of an outpatient psychiatric service in patients with bipolar disorder. Furthermore, it is the first time that mood instability is included as an outcome measure in an RCT investigating the effect of smartphone-based monitoring and treatment. The SmartBipolar trial will provide unique experiences of implementation of smartphone-based treatment for future trials and clinical practice in other psychiatric disease areas. A central aspect of the present SmartBipolar trial will be that patients with bipolar disorder are encouraged to conduct daily self-evaluations of symptoms. Firstly, this will empower the patients themselves (and their relatives) by increasing self-insight and self-treatment. Secondly, this will empower the clinicians by providing ongoing daily patient data increasing knowledge of the patient state and adherence to treatment between out-patient visits making early support and individualized treatment intervention possible. Finally, this study setup will facilitate research by providing continued and fine-grained daily patient-reported and automatically generated smartphone-based data on illness and treatment and thereby allowing for detailed and fine-grained identification of patterns.

### Hypotheses

In patients with bipolar disorder receiving specialized outpatient treatment for patients with bipolar disorders, using daily smartphone-based monitoring and treatment, *including* clinical feedback, improves mood instability and other clinically relevant outcomes (specified below) more than daily smartphone-based monitoring *without* clinical feedback or daily smartphone-based mood monitoring *only*.

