### Objectives

The objectives are as follows: to investigate in a randomized controlled parallel-group trial whether (1) daily smartphone-based outpatient monitoring and treatment *including* clinical feedback versus (2) daily smartphone-based monitoring *without* clinical feedback or (3) daily smartphone-based mood monitoring *only* improves mood instability in patients with bipolar disorder and, furthermore, to investigate if daily smartphone-based monitoring, *including* clinical feedback, improves *questionnaire-based* quality of life, self-rated depressive symptoms, self-rated manic symptoms, perceived stress, and satisfaction with care, as well as *register-based* risk of psychiatric hospitalization and cumulated days of psychiatric admission as compared with daily smartphone-based monitoring *without* clinical feedback and daily smartphone-based mood monitoring *only* in patients with bipolar disorder. In addition, this is to investigate if daily smartphone-based monitoring, *including* clinical feedback, improves *smartphone-based* measures of stress, anxiety, irritability, activity, sleep duration, days with adherence to medication, days without mixed mood, and adherence to smartphone-based monitoring as compared with daily smartphone-based monitoring *without* clinical feedback in patients with bipolar disorder.

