#### The clinical feedback

By offering all patients with bipolar disorder and clinicians to use the system, a unique world class data set is made, which can be used to optimize treatment to the benefit of patients and clinicians. Nevertheless, it is unclear and has never been investigated how smartphone-based treatment is best optimized—with or without a clinical feedback loop. The clinical feed-back loop includes (1) that clinicians continuously monitor self-reported patient smartphone data making early intervention possible when data suggest deterioration; (2) actively support and help patients employing the Monsenso tools including psychoeducation, personal treatment plans, and cognitive behavioral therapy tools; (3) integration of the Monsenso system in group-based psychoeducation courses in the CAG bipolar clinics; and (4) meetings with the staff from the entire CAG bipolar clinic on a weekly basis where Monsenso registrations are monitored and discussed in collaboration (board meetings).

It is possible that patients will be able to use the Monsenso system entirely as a self-help tool in addition to treatment in the CAG bipolar clinics (see first control group below).

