### The control group

#### The first control group

Patients allocated to the first control group are invited to conduct daily smartphone-based monitoring *without* a clinical feedback loop. Furthermore, they will have full access to the smartphone-based CBT modules as described above.

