#### The second control group

Patients allocated to the second control group are invited to conduct daily smartphone-based mood monitoring only.

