The primary outcome is mood instability between the intervention group and the two control groups—calculated as described above. Analyses will be done using intention-to-treat analyses. According to recent analyses, [15] mood instability in patients with bipolar disorder calculated using the definition above has a mean of 0.80 (SD 1.93). If mood instability decreases 0.2 units (SD 0.53) on the mood instability scale for trial arm I (the intervention group) versus trial arm II (the first control group) and trial arm I versus trial arm III (the second control group), respectively, a drop-out rate of 10% during the 6-month trial period (in accordance with the drop-out in our prior 6 months smartphone RCT) [30], a two-sided risk of type 1 error, *α* of 0.025 (since we will conduct two analyses between three groups with 0.05 level of significance in each analyses), a type 2 error risk, *β*, and a statistical power of 80%, the sample size (*N*) is calculated as *N* = 183. Thus, we need to allocate 67 patients in each of the tree arms of the trial and to randomize a total of 201 patients in the SmartBipolar trial.

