### Perspectives

The learning potential of the SmartBipolar trial is high due to its novelty, originality, and pragmatic design. The SmartBipolar trial is the first to investigate the effects of add-on smartphone-based treatment in mood instability for patients with bipolar disorder. The study findings will directly be implemented in the CAG bipolar outpatient clinics, potentially in a revised version according to the study findings. Moreover, findings will have great influence on the area of implementation of IT solutions in the mental health services in Denmark and internationally.

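### The plan does not say which of its two control contrasts must succeed, or that only intervention versus control group 1 answers the clinical feedback question

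*Protocol article*

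**What the plan says.** The Hypotheses section of the protocol article says that monitoring and treatment with clinical feedback improves mood instability and other outcomes "more than daily smartphone-based monitoring *without* clinical feedback or daily smartphone-based mood monitoring *only". The first objective uses the same connective for the primary outcome: "daily smartphone-based monitoring *without* clinical feedback or (3) daily smartphone-based mood monitoring *only* improves mood instability". For the questionnaire and register outcomes, Objectives switches to 'and': "as compared with daily smartphone-based monitoring *without* clinical feedback and daily smartphone-based mood monitoring *only* in patients with bipolar disorder".

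The Mood instability subsection of the sample size section first describes the comparison in one phrase: "The primary outcome is mood instability between the intervention group and the two control groups". It then sizes arm I versus arm II and arm I versus arm III separately, each at two-sided 0.025 because two analyses will be done.

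The two controls differ in content. Both arm I and arm II are invited to rate all symptoms daily. Of arm II the article adds: "Furthermore, they will have full access to the smartphone-based CBT modules as described above". Of arm III it says: "Patients allocated to the second control group are invited to conduct daily smartphone-based mood monitoring only". The section on the clinical feedback gives the motivating question: "it is unclear and has never been investigated how smartphone-based treatment is best optimized—with or without a clinical feedback loop".

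**The concern.** The two contrasts answer different questions. I versus II compares the full system with and without the feedback loop, so it isolates feedback. I versus III compares feedback, CBT modules and wider symptom monitoring, all together, with mood rating alone.

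The hypothesis joins both controls under one statement about treatment that includes feedback, and no section says how the two results combine. If only I versus III succeeds, one reader could say that the hypothesis is confirmed and another that it is not, and the choice could be made after the results are seen. The article itself allows for this case: the section on the clinical feedback says that patients may be able to use the system purely for self-help.

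The decision has practical weight. Feedback is the part that takes staff time (continuous review of patient data and weekly clinic meetings), and the Perspectives section says: "The study findings will directly be implemented in the CAG bipolar outpatient clinics".

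**Working it through.** **Inputs.** From the Mood instability subsection: difference 0.2, SD 0.53, two-sided alpha 0.025 per contrast, power 80%, N = 183 (183/3 = 61 per arm), 201 randomised (67 per arm). Allocation is 1:1:1 (Trial design). Assumptions made here: normal test statistics, and a correlation of 0.5 between the two contrasts because they share arm I and the arms are equal in size.

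**The plan's own figure.** The usual two-sample formula gives n per arm = 2 × [(2.241 + 0.842) × 0.53/0.2]² = 133.5, so 134 per arm, not 61. N = 183 is therefore not reproduced. That is a separate matter. The results below use 61, as the plan states, with 134 as a check.

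**Power of one contrast at 61 per arm.** SE = 0.53 × √(2/61) = 0.0960. The expected z is 0.2/0.0960 = 2.084. Power = P(Z > 2.241 − 2.084) = 43.7% (44% below).

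**Joint results.** P(both) comes from the bivariate normal distribution with correlation 0.5. P(either) = P(I vs II) + P(I vs III) − P(both). P(only I vs III) = P(I vs III) − P(both). A success is a significant result that favours the intervention.

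| Per arm | True I−II | True I−III | I vs II | I vs III | Both | Either | Only I vs III |
|---|---|---|---|---|---|---|---|
| 61 | 0.2 | 0.2 | 43.7% | 43.7% | 27.3% | 60.2% | 16.4% |
| 61 | 0 | 0.2 | 1.2% | 43.7% | 1.1% | 43.9% | 42.6% |
| 134 | 0.2 | 0.2 | 80.2% | 80.2% | 68.9% | 91.4% | 11.2% |
| 134 | 0 | 0.2 | 1.2% | 80.2% | 1.2% | 80.2% | 78.9% |

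In the first row, 60.2% − 27.3% = 32.9% of trials give a split result. Half of these (16.4%) are wins on I versus II alone, which do support feedback. The pattern in dispute is the other half.

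**Holm in place of a fixed 0.025 each.** The smaller p is tested at 0.025 and, if rejected, the other at 0.05. By simulation at 61 per arm with both differences 0.2, power for I versus II rises from 43.7% to 48.6%, and for both from 27.3% to 37.0%. The chance of at least one success stays at 60.2%, because the first step is the same. With no true differences, the chance of at least one two-sided rejection is 4.6% under either procedure, again because of the shared first step. Holm keeps family-wise error at or below 5% in general.

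**The case against.** The strongest reply is that no one-win rule exists. In a comparative sentence, better than A or B commonly means better than each, and on that reading Hypotheses and Objectives agree. This stands. A reader might infer from the 'or' that success on either contrast confirms the hypothesis, but the text does not say so.

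A reader might also infer that the primary hypothesis and the primary objective contradict each other. They do not: both use 'or' for mood instability, and the 'and' belongs to the questionnaire and register outcomes. Nor does the split alpha prove an either-wins rule, since it fits equally well with two contrasts that each carry their own claim.

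The misattribution also needs a further step. The Limitations section concedes that the effects of individual components cannot be separated, the article commits to publishing all findings, and the Perspectives sentence goes on to allow a revised version in light of the results. The 43% (and 79% at 134 per arm) is almost entirely genuine power for a true I versus III difference, under an assumed zero effect of feedback. It misleads only if the result is then credited to feedback. A split result is a minority outcome at the planning inputs.

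Finally, detail on combining tests often sits in an analysis plan, and 0.025 per contrast is a valid procedure. Both points are fair. What remains is that the article's own hypothesis covers two different questions, and nothing in it ties the feedback claim to the one contrast that can support it. The concession in Limitations does not fill the gap: it sets no bound on what I versus III may be taken to show, and it passes over the fact that I versus II does isolate the feedback loop.

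**Conclusion.** The point holds as an ambiguity that should be closed before analysis. It is not an explicit rule that one win is enough. At the article's inputs and 61 evaluable per arm, the troublesome result (I versus III succeeds, I versus II does not) occurs in about 16% of trials if both true differences are 0.2. It occurs in about 43% if feedback adds nothing and the rest of the package gives 0.2; that scenario is an assumption made here, not the planning case. These figures rest on normal tests, a common SD of 0.53, a correlation of 0.5 and 0.025 per contrast.

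The ambiguity would remain if the sample size were corrected. It is also separate from the conflict between 0.025 in the sample size section and 0.05 for all analyses in Statistical methods, although the fix should settle that level for the primary pair as well.

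**What to change.** State the following in Hypotheses, Objectives and Statistical methods:

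1. A claim that clinical feedback improves mood instability rests on arm I versus arm II.
2. Arm I versus arm III supports only a claim for the whole package over mood monitoring.
3. Superiority to both controls is claimed only if both contrasts are rejected.
4. The two primary contrasts are tested by Holm: the smaller p against 0.025 and, if it is rejected, the other against 0.05.

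Holm replaces the fixed 0.025 for each contrast. It is an improvement rather than the correction of an error. No new patients or data are needed, and the article reports recruitment as ongoing with no interim analyses.

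There are two costs. The full hypothesis will be declared confirmed less often than under an either-wins reading: about 37% with Holm against 60% at the stated inputs. And if feedback truly adds nothing while the package gives 0.2, Holm raises the chance of a false finding for feedback (in the favourable direction, 61 per arm) from 1.2% to 2.3%, still within the 5% family-wise limit.
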